## Abstract

**Background:**

Cancer patients experience psychological and social distress due to their medical treatment and social issues. However, continuous and specialized social support is still lacking. In Germany, a group of company health insurance funds has developed an approach to support cancer patients with monthly structured interviews conducted by specially trained Social Care Nurses. The nurses will identify patient needs in order to provide help with medical, personal, and social matters. One aim of the scientific evaluation is to analyze the effect of the consultations on various patient-reported outcomes, especially quality of life. The evaluation concept will be described in this study protocol.

**Methods/design:**

The evaluation is a non-randomized, controlled, multi-center intervention study with a mixed-method design. It consists of three research modules which include primary data from questionnaires, and claims data from the health insurance funds. In Module 1, cancer patients will be recruited to form an intervention group (OSCAR, *n* = 150) and a control group (*n* = 200) in four study centers for a period of 1 year. One baseline and three follow-up questionnaires will be conducted to survey the patient-reported outcomes. Relevant secondary outcomes are health literacy, participation, and physician-patient communication. In Module 2, claims data will be used to analyze cost effects and thereby assess effectivity and hospitalization. Module 3 will involve a qualitative analysis of project diaries kept by the Social Care Nurses. The diaries will record the nurses’ practical experiences and the benefits of deploying OSCAR across the German healthcare system.

**Discussion:**

OSCAR is an innovative way of providing cancer patients with continuous support to improve their quality of life. The evaluation concept aims to assess the effects of the monthly consultations by the Social Care Nurses on the patients, and will use a mixed-method design. The results are important for assessing the transferability of OSCAR to the healthcare system as a whole.

**Trial registration:**

German Clinical Trials Register (DRKS-ID: DRKS00013640). Registered 29 December 2017.

## Background

### Demand for social support for cancer patients

Cancer cause a high number of incident cases in Germany every year (229,920 women and 252,550 men in 2013) [1]. Due to the progression of the diseases, patients and their relatives experience distress caused by medical treatment and social issues [2, 3]. The misunderstanding of the disease can lead to inappropriate self-assessments of one’s prognosis and a choice of unsuitable medical treatments [4]. Simultaneously, patients receive overtreatment even though they have an incurable disease [5]. In these situations, palliative care could be appropriate for improving quality of live [6]. Enhancing palliative care can help patients to find suitable medical treatments that can increase quality of life. However, the specific needs of cancer patients are not taken into adequate account by the healthcare system because of a lack of palliative care [7]. Currently, patient navigation programs are used to help patients with medical, nursing, psychological, and healthcare-related issues. Recent studies have attempted to evaluate the impact of these programs (such as *Onkolotse* by the Saxon Cancer Society) [8, 9]. In this context, patient-reported outcomes (PROs) are very important for examining the subjective benefit of interventions from the patient’s perspective, with the focus on relevant outcomes (e.g. quality of life) [10].

### Development of the OSCAR project

The Oncological Social Care Project (OSCAR) was developed by the German company health insurance fund Pronova BKK. The concept is based on the Saxon Cancer Society’s *Onkolotse* navigation program for cancer patients. An essential component of OSCAR is the additional social support provided by the Social Care Nurses (SCNs), who aim to identify deficits in healthcare utilization by cancer patients and support them in relevant areas (e.g. the medical treatment of the cancer, psychosocial support for anxiety, practical tips regarding social security services, and organization of rehabilitation). Moreover, the SCNs are regular and accessible contact partners in a complex and fragmented multidisciplinary treatment process. Each patient is accompanied for 1 year, regardless of whether they are being treated as inpatients or outpatients, or are currently not receiving any therapy. The intervention aims to access and improve the quality of life for patients with advanced cancer and a poor prognosis. It uses twelve structured interviews over the course of 1 year. The SCNs received training from the Saxon Cancer Society. OSCAR is implemented by five SCNs at four locations.

## Methods

The OSCAR evaluation is a mixed-method study consisting of three research modules. Modules 1 and 2 involve a non-randomized, controlled, multi-center intervention study which compares primary data from regularly conducted questionnaires and claims data from German statutory health insurance funds in the intervention and control groups. In addition, a qualitative content analysis is planned in module 3 and will be based on the project diaries completed by each SCN. The analysis will assess OSCAR’s effectivity and the benefit of implementing it in the German healthcare system (Fig. 1).

**Fig. 1 Fig1:**
[figure not shown]
Modules in the OSCAR evaluation concept

### Study objectives

Primary objective:

To compare quality of life over study period between the intervention group (patients who had met an SCN) and the control group (Module 1).

Secondary objective:
To compare the health literacy, participation, and physician-patient communication in the intervention and control groups (Module 1)To explore the associations between quality of life and health literacy, participation, and physician-patient communication (Module 1)To compare the incidence rate of outpatient visits in both groups (Modules 1 and 2)To compare the healthcare costs in both groups (Module 2)To assess the SCN’s practical experiences (Module 3)

### Inclusion and exclusion criteria for participation in the evaluation survey in modules 1 and 2

Inclusion criteria:
Aged ≥18 yearsAt least a combination of one type of cancer and one operation and procedure, as defined by the ICD and OPS codes listed in Additional file 1

Exclusion criteria:
Advanced dementiaAcute addictions

### Module 1: primary data, patient-reported outcomes

#### Participant recruitment

The recruitment was carried out in four different hospitals with oncology departments across three cities in two states in Germany. Two of the hospitals are located in Berlin, while the other two are in Leverkusen and Duisburg.

In all four study sites, the SCNs recruited BKK-insured patients for the intervention group by obtaining informed consent. The SCNs are responsible for the monthly consultations to support the patients in the intervention group. Patients who are insured with a different provider were recruited by Study Nurses (SNs) for the control group. The SNs’ main task is to conduct the evaluation questionnaires in both study groups up to four times within 1 year. The evaluation’s baseline survey will be conducted after recruitment (t0) and followed up after 90 (t1), 180 (t2), and 365 (t3) days. The patients can choose between personal, telephone, and postal interviews, depending on their health status and which method is most comfortable for them. Dividing responsibilities between SCNs and SNs is necessary to ensure the independence of the evaluation surveys. Patients in both groups were recruited at the same study sites between February 2018 and the end of February 2019.

#### Questionnaire

The items for the evaluation questionnaire are listed in Table 1:

**Table 1 Tab1:** Items in the evaluation questionnaire

Item	Description
Quality of Life of Cancer Patients (EORTC QLQ-C30) [11]	The EORTC QLQ-C30 is a questionnaire for measuring health-related quality of life, and is provided by the European Organisation for Research and Treatment of Cancer. Patients are asked to answer 30 questions, which address e.g. physical, emotional, cognitive, and social issues. 28 items have four response options. Two items for the global health status and the quality of life have a seven-point scale. The EORTC QLQ-C30 consists of five functional scales and three symptom scales. In addition, a global health status (QoL) scale as well as six single items. All of the scales and the single items will use a linear transformation to standardize the raw score. The scores range from 0 to 100.
Illness Perception Questionnaire (IPQ) [12]	The IPQ consists of 64 items on 8 scales, and measures the individual’s beliefs and feeling about their illness. The illness coherence subscale consists of five items and is used for the evaluation questionnaire in this study. The scores will be summed and divided by the number of items.
Patient Reaction Assessment (PRA-D) [13]	The PRA-D is a self-description instrument to record the patient-perceived quality of the relationship between patients and physicians. In this study, we adapted five communication questions to a five-point Likert scale (from 1 = “I strongly disagree” to 5 = “I strongly agree”).
German modified version of the Autonomy Preference Index (API-Dm) [14]	The API-Dm measures patients’ preferences for participation and information regarding medical decisions. Patients are asked to answer eleven questions using a four-point Likert scale (from 0 = “strongly disagree” to 4 = “strongly agree”). The information preference consists of seven items, with scores ranging from 0 to 28. The participation preference consists of four items, with scores ranging from 0 to 16. The total score of each patients’ preference will be transformed into scores ranging from 0 to 100.
Decisional Conflict Scale (DCS-10) [15]	The DCS-10 is a self-reported questionnaire, which allows an evaluation of decision conflicts among patients. The short version of the DSC comprises ten items grouped into four subscales: uncertainty, information, values clarity, and support decision. Each item is measured on a three-point Likert scale (0 = “yes”, 2 = “unsure”, 4 = “no”). Scores range from 0 (no decision conflict) to 100 (extremely high decision conflict).
European Health Literacy Survey (HLS-EU-Q6) [16]	The HLS-EU-Q6 is the short version of the 47-question European Health Literacy Survey. It is divided into three areas: healthcare, disease prevention, and health promotion. Each of the six questions has five possible responses. A mean score is calculated and allocated to one of three categories: insufficient health literacy (range 1–2), problematic health literacy (2–3), and sufficient health literacy (3–4).
Medical Care Utilization [17]	Medical care will be assessed by the frequency of utilization of different therapies and physician groups.
Oslo Social Support Scale (OSSS-3) [18]	The OSSS-3 is a brief measurement of social support. It consists of three questions that address the number of close people, interest and concern from other people, and practical help from neighbors. The scores range from 3 to 14 and will be categorized into three groups: 3–8 indicates poor support, 9–11 shows moderate support, and 12–14 reflects strong support.

Further instruments are used to measure sociodemographic variables, especially with regard to age, sex, migration status, and social status [19–21]. Finally, participants in the intervention group will be asked to evaluate their contact with the SCN for the last 3 months. The items are related to specific consultation topics and whether or not the support was useful for the respective topic. Participants will also be asked about the quality and quantity of contact with the SCN.

### Statistics

#### Sample size calculation

A sample size of 100 participants in the intervention group and 150 in the control group will reach a power of 80% at a two-sided level of significance of 5% to detect a difference in the EORTC QLQ-C30 (scores range from 0 to 100) with a Cohen’s d effect size of 0.4 (mean difference of ten scores and standard deviation (SD) of 25 scores) [11]. Given that the effect size might be smaller due to a lower mean difference or higher SD, and that the severity of cancer can cause higher dropout rates, we aim to include 150 participants in the intervention group and 200 in the control group (so a total sample size of 350 participants).

The sample size calculation based on the t-test was used in spite of the intended analysis with a baseline-adjusted repeated-measures linear mixed model (ANCOVA, three-level random intercept model to account for repeated measures in patients and clustering in centers). It can be shown [22] that a conservative approach for estimating sample sizes has the same power as a t-test with n subjects where p is the variance deflation factor, calculated by the correlation of baseline and follow-up measures. Assuming the worst case of *p* = 0 leads to the sample size based on the t-test.

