#### Statistical analysis plan

All statistical tests are performed using Stata IC15 (StataCorp, 2017, College Station, TX, USA). The primary hypothesis will be tested at a two-sided significance level of α = 0.05. All secondary hypotheses will be tested within an exploratory framework.

Descriptive statistics and the number of participants reflected in the calculation (n) will be presented in each group. For continuous variables, mean with SD for normal distribution and median with interquartile range (IQR) for other distribution variables will be presented. For categorical data, frequencies and percentages will be displayed for each category. Graphic methods such as box plots and line graphs will be used for visualizing the data.

The comparison of EORTC QLQ-C30 (global health status as a primary outcome), physician-patient communication (scores), health competence (scores), participation (scores), and knowledge (scores) over the study period between the groups will be reported as mean and 95% CI, and performed using a linear mixed model (LMM) with three levels over all available time points. Random intercepts for the patient ID and for the study clinics are included in the model to account for the cluster structure of the data. To keep selection bias to a minimum, we will develop a propensity score for adjusting baseline factors. The propensity score will be used with the inverse probability of treatment weighting (IPTW) method because the results from this method are similar to a randomized trial [23, 24].

The number of outpatient visits will be counted and the study time will be calculated over the follow-up time for each patient. The incidence rate of outpatient visits per person-time will be presented, and Poisson regression will be used to compare the incidence rate between groups.

All outcomes will be analyzed using modified intent-to-treat populations including all subjects who receive at least one consultation from an SCN and for whom at least the first follow-up assessment at Visit 1 (at 3 months) is available.

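### The stated inputs give 87% power for 100 + 150 participants, not the stated 80%; the discrepancy is conservative and needs one sentence reworded

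*Protocol article*

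**What the plan says.** In the protocol article, Module 1, under Sample size calculation, the planning statement is: "A sample size of 100 participants in the intervention group and 150 in the control group will reach a power of 80" per cent, "at a two-sided level of significance of 5" per cent. The effect is a Cohen's d of 0.4, spelled out as a "mean difference of ten scores and standard deviation (SD) of 25 scores". The next paragraph says that the calculation rests on the t-test although a baseline-adjusted mixed model is planned, and that the correlation between baseline and follow-up is set to its worst case of zero, so no precision is credited to baseline adjustment.

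The Module 1 Statistical analysis plan repeats the level: "The primary hypothesis will be tested at a two-sided significance level of α = 0.05". It plans a linear mixed model with random intercepts for patient and clinic, combined with inverse probability of treatment weighting (IPTW).

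The enrolment target is a separate, later step. Because the effect might be smaller, the SD larger, and because "severity of cancer can cause higher dropout rates, we aim to include 150 participants in the intervention group and 200 in the control group", the total becomes 350.

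**The concern.** The paragraph gives everything that a two-sample t-test calculation needs: both group sizes, difference, SD, level, sidedness, test and power. The figures should therefore reproduce one another, and they do not. The stated group sizes are too large for 80% power, or the stated power is too low for the group sizes.

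This is the planning statement for the primary outcome. A reader who wants to know how much loss of precision the design can absorb, for instance through weighting, would conclude from the printed 80% that 100 + 150 has no slack at d = 0.4. On the stated inputs it has some.

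**Working it through.** **Inputs, all from Sample size calculation:** n1 = 100, n2 = 150; difference 10, SD 25, so d = 10/25 = 0.4, which agrees with the stated d; two-sided 5%; two-sample t-test; no gain from baseline correlation.

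**Formula.** Noncentrality = d / √(1/n1 + 1/n2), with n1 + n2 − 2 degrees of freedom. Power is the probability that the noncentral t statistic exceeds the two-sided 5% critical value. The normal approximation is Φ(noncentrality − 1.960).

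**The plan's own figure.** √(1/100 + 1/150) = √0.016667 = 0.1291, and 0.4 / 0.1291 = 3.098 with 248 degrees of freedom. The normal approximation is Φ(3.098 − 1.960) = Φ(1.138) = 87.3%. The exact t-test gives 87.0%. The stated 80% is not reproduced.

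**Which sizes give 80%?**

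| Group sizes | Noncentrality | Power, exact t | Power, normal |
|---|---|---|---|
| 100 + 150 | 3.098 | 87.0% | 87.3% |
| 100 + 100 | 2.828 | 80.4% | 80.7% |
| 99 + 99 | 2.814 | 79.97% | 80.4% |
| 83 + 124 | 2.820 | 80.2% | 80.5% |
| 82 + 123 | 2.806 | 79.7% | 80.1% |
| 150 + 200 (target, no loss) | 3.703 | 95.8% | 95.9% |

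By the exact t-test, 100 per group is the smallest equal allocation that reaches 80%. At 2:3, about 83 + 124 does.

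**What 100 + 150 detects with 80% power.** Normal approximation: (1.960 + 0.842) × 25 × 0.1291 = 9.04 points. Exact t: d = 0.363, that is 0.363 × 25 = 9.1 points at SD 25 or, with the difference kept at 10, an SD of 10/0.363 = 27.5.

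**Which changed inputs would give about 80% with 100 + 150?**

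- Two-sided level of 2.5%: 79.99%. Both places that state the level say 5%.
- Variance inflation of 1.2 (effective sizes 83.3 + 125): 80.4%; at 1.22, 79.7%. No inflation factor is stated.
- Loss of 15% or 20% taken out of 100 + 150: 81.2% or 78.8%. The article deals with dropout separately, by raising the target.
- A Wilcoxon test at its worst-case efficiency of 0.864: 81.8%. The article names the t-test.

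A one-sided 5% test moves the wrong way, to 92.6%.

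**The case against.** **The sentence may mean at least 80%.** On that reading it is not false, and this stands in part. But 100 + 150 is then not the size that the stated inputs yield for 80%, and the following paragraph presents it as the t-test result.

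**An unstated assumption may lie behind the figure.** This is possible. A variance inflation of about 1.2 would be a reasonable one for a weighted analysis. The article does not state it, so it can be asked for but not presumed. A reader might also infer that 80% was carried over from a calculation with 100 per group, since that is exactly the smallest equal allocation. The coincidence is suggestive, but nothing in the article documents it.

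**The consequence is small.** This stands. The discrepancy is conservative, recruitment is reported as carried out up to the end of February 2019, and the group comparison is to be reported with a 95% confidence interval, which shows what a null result excludes whatever planning power was printed.

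**Stronger readings that the article does not support.** Three inferences are tempting:

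- The step from 100 + 150 to 150 + 200 could be read as a dropout allowance of 50/150 = 33% in one group and 50/200 = 25% in the other, unequal without a reason. The article states no dropout fraction. It gives one joint reserve for a smaller difference, a larger SD and dropout, and a rate per group is detail that a condensed article may leave to the full protocol.
- It might seem that dropout could use up the whole reserve and leave nothing for a smaller effect or larger SD. The figures contradict this: if only 100 + 150 remain, power is still 80% for 9.1 points, or for 10 points at an SD of 27.5.
- It might seem that the detectable difference is misstated. The article gives 10 points as the planning effect and does not call it the smallest detectable difference.

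**Conclusion.** The stated power and the stated group sizes do not belong together. On the article's inputs, 100 + 150 gives 87.0% rather than 80%, and 80% belongs to 100 + 100 or about 83 + 124. This is a reporting error in the planning statement, conservative in direction and minor in effect. It does not make the trial underpowered on its own assumptions and gives no reason to change enrolment or analysis.

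The 87% is the power of an unweighted, unclustered two-sample t-test with d = 0.4 and no credit for baseline adjustment. It is not the power of the planned analysis. IPTW usually reduces the effective sample size, while baseline adjustment and repeated measures may restore some precision; the article quantifies neither. If the net effect were a variance inflation of about 1.2, taken here as an assumption, power would be back near 80%.

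**What to change.** Replace the power sentence under Sample size calculation with wording such as:

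> By a simple two-sample t-test, without allowance for IPTW or clustering by clinic, 100 and 150 analysed patients give 87% power for d = 0.4 (80% power for 9.1 points at SD 25, or for 10 points at an SD of about 27.5).

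Alternatively, keep 80% and state the extra assumption that produced it, for example a variance inflation of about 1.2. The caveat on IPTW and clustering should stay in the first version, because 87% on its own could be taken as the power of the weighted mixed model.

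The cost is one sentence. The target of 150 + 200, the primary outcome and the analysis are unaffected.

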#### Statistical analysis plan

All statistical tests are performed using Stata IC15 (StataCorp, 2017, College Station, TX, USA). The primary hypothesis will be tested at a two-sided significance level of α = 0.05. All secondary hypotheses will be tested within an exploratory framework.

Descriptive statistics and the number of participants reflected in the calculation (n) will be presented in each group. For continuous variables, mean with SD for normal distribution and median with interquartile range (IQR) for other distribution variables will be presented. For categorical data, frequencies and percentages will be displayed for each category. Graphic methods such as box plots and line graphs will be used for visualizing the data.

The comparison of EORTC QLQ-C30 (global health status as a primary outcome), physician-patient communication (scores), health competence (scores), participation (scores), and knowledge (scores) over the study period between the groups will be reported as mean and 95% CI, and performed using a linear mixed model (LMM) with three levels over all available time points. Random intercepts for the patient ID and for the study clinics are included in the model to account for the cluster structure of the data. To keep selection bias to a minimum, we will develop a propensity score for adjusting baseline factors. The propensity score will be used with the inverse probability of treatment weighting (IPTW) method because the results from this method are similar to a randomized trial [23, 24].

The number of outpatient visits will be counted and the study time will be calculated over the follow-up time for each patient. The incidence rate of outpatient visits per person-time will be presented, and Poisson regression will be used to compare the incidence rate between groups.

All outcomes will be analyzed using modified intent-to-treat populations including all subjects who receive at least one consultation from an SCN and for whom at least the first follow-up assessment at Visit 1 (at 3 months) is available.

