One advantage of the evaluation is the mixed-method design, which includes patient-reported outcomes, claims data from health insurance funds, and qualitative analyses of the SCNs’ project diaries. To evaluate the effects of continuous SCN support in Module 1, a prospective, non-randomized, multicenter, longitudinal study design was applied. Our patients were not assigned randomly, due to the limitation of the SCNs, who were trained and supported by the BKK insurance fund. Since randomization was not carried out, we are concerned about selection bias. Therefore, the baseline characteristics will be compared and we will control for baseline imbalance by using propensity score in our analysis. The propensity score with the inverse probability of treatment weighting (IPTW) method will be applied because the results from this method are similar to a randomized trial [23, 24]. For Module 2, we will match the intervention and control cases in order to reduce bias and confounding factors as much as possible. Moreover, given the severity of the patients’ conditions, we aimed to reduce the interview time by using the short versions of the instruments, if available, rather than applying generic instruments. In conclusion, we believe our study provides healthcare support for cancer patients. Hopefully, it can be applied for other severe chronic diseases. The evaluation of OSCAR is currently ongoing. In terms of providing healthcare support according to the patient’s needs, we expect our study to show that SCN support has a positive effect on the patient’s quality of life, health literacy, and participation in therapy planning.

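### Study clinic is a random intercept with only four clinics, so its variance is poorly estimated and the term guards only partly against between-clinic confounding

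*Protocol article*

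**What the plan says.** The clinic term is an explicit choice, made twice in the Module 1 Statistics section of the protocol article. The Statistical analysis plan states: "Random intercepts for the patient ID and for the study clinics are included in the model". The Sample size calculation describes the same structure, a "three-level random intercept model to account for repeated measures in patients and clustering in centers", fitted with baseline adjustment. The purpose given for the term is to reflect clustering; it is not presented as a control for confounding.

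Participant recruitment fixes the number of clinics: "The recruitment was carried out in four different hospitals with oncology departments across three cities in two states in Germany". It also says "Patients in both groups were recruited at the same study sites between February 2018 and the end of February 2019". BKK-insured patients enter the intervention group and patients of other insurers the control group, so group varies within each clinic and is set by insurer. The Discussion confirms it: "Our patients were not assigned randomly, due to the limitation of the SCNs".

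Confounding is left to weighting: "To keep selection bias to a minimum, we will develop a propensity score for adjusting baseline factors". The article does not list the factors in that score. On the test itself: "The primary hypothesis will be tested at a two-sided significance level of α = 0.05". It gives no clinic ICC, no group share by clinic and no expected difference in quality of life between clinics.

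**The concern.** Two things go wrong when four clinics are treated as a random sample.

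First, the model has to estimate a clinic variance from four units. That estimate is very imprecise and often falls on zero. When it does, the clinic term drops out and the model pools across clinics.

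Second, a random intercept treats clinic effects as independent of group. Nothing in this design ensures that. The BKK share at each hospital depends on the local insurance mix. A hospital with more BKK patients may also treat sicker or healthier patients, and part of that difference then passes into the group effect.

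At stake is the primary estimate, in a study that names selection bias as its main weakness. Since both groups are recruited at the same sites, a comparison made wholly within clinics is available and would remove this source of bias. The planned model uses it only in part.

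**Working it through.** **Inputs from the protocol article.** Four clinics; 100 + 150 = 250 patients in the power statement (62.5 per clinic); 150 + 200 = 350 as the recruitment target (87.5 per clinic); SD 25; planned difference 10; two-sided 5%.

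**Assumptions, not in the article.** Clinic ICC 0.01 to 0.10; equal clinic sizes; intervention shares by clinic as given below; clinic means rising in line with those shares.

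**The plan's own figure.** The plan gives no figure for the clinic variance. The nearest is 80% power with 100 against 150 patients. SE = 25 × √(1/100 + 1/150) = 3.23; 10/3.23 − 1.96 = 1.14; power is about 87%. The stated figure is conservative and does not bear on this point.

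**Step 1: precision of a variance from four units.** Even with error-free clinic means, the 95% interval runs from 3/9.348 = 0.32 to 3/0.2158 = 13.9 times the estimate.

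**Step 2: chance that the variance is estimated as zero.** With r = 1 + n × ICC/(1 − ICC), the chance is P(χ² on 3 df < 3/r) for REML and P(χ² on 3 df < 4/r) for ML.

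| Patients per clinic | ICC | r | REML | ML |
|---|---|---|---|---|
| 62.5 | 0.01 | 1.63 | 39% | 52% |
| 62.5 | 0.02 | 2.28 | 28% | 38% |
| 87.5 | 0.01 | 1.88 | 34% | 45% |
| 87.5 | 0.02 | 2.79 | 22% | 30% |

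**Step 3: how much confounding the random intercept lets through.** Take shares of 20, 35, 50 and 60%.
- Mean share: 0.4125.
- Between-clinic variance of group: B = 0.0230.
- Mean within-clinic variance of group: W = (0.16 + 0.2275 + 0.25 + 0.24)/4 = 0.2194.
- Slope of clinic mean on share: s = 5/0.40 = 12.5 or 10/0.40 = 25.
- With λ = σ²/(σ² + nτ²), the bias of the group effect is s × λB/(W + λB).

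With no clinic term λ = 1, giving 12.5 × 0.0230/0.2423 = 1.18 points, or 2.37 for the wider span. With fixed clinic effects λ = 0 and the bias is 0. The random intercept lies between. The assumed clinic means imply τ² = s² × B × 4/3 = 4.79 or 19.1. At 62.5 per clinic, λ = 0.68 or 0.34 and the bias is 0.83 or 0.87. At 87.5 per clinic, λ = 0.60 or 0.27 and the bias is 0.74 or 0.69.

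Those values treat τ² as known. When it is estimated, simulation of the same scenario gives about 0.7 to 1.1 points with type I error of about 5 to 8%. With fixed effects the bias is near 0 and type I error about 5 to 6%. The bias moves by about 0.1 with the spacing of the clinic means.

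**Step 4: wider range.** Simulated bias in points; 350 patients, no true effect, 1,500 trials per row, one value per patient, no weighting or baseline adjustment.

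| Shares (%) | ICC | No clinic term | Random, ML | Random, REML | Fixed |
|---|---|---|---|---|---|
| 25/35/50/62 | 0.01 | 1.41 | 0.85 | 0.67 | −0.03 |
| 25/35/50/62 | 0.02 | 2.09 | 0.96 | 0.74 | 0.01 |
| 25/35/50/62 | 0.05 | 3.32 | 0.76 | 0.58 | 0.03 |
| 25/35/50/62 | 0.10 | 4.65 | 0.56 | 0.43 | 0.04 |
| 15/30/55/72 | 0.01 | 2.19 | 1.44 | 1.14 | −0.05 |
| 15/30/55/72 | 0.02 | 3.13 | 1.69 | 1.29 | 0.00 |
| 15/30/55/72 | 0.05 | 5.07 | 1.37 | 1.01 | 0.01 |

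The random intercept removes between 34% (1 − 1.44/2.19) and 91% (1 − 0.43/4.65) of the bias. Its type I error is about 5 to 11%, against 3.9 to 5.5% with fixed effects. With equal shares of 43% in every clinic, all models have bias near zero and type I error of about 4 to 6%.

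**Step 5: price of fixed effects.** Against a model without clinic, the SE rises by at most √(0.2423/0.2194) = 1.05 in the Step 3 scenario. Under the strong imbalance at ICC 0.01 the mean SE is 3.02, against 2.80 for REML (8% more) and 2.75 for ML (10% more). Part of that gap is understatement by the random-intercept model: the estimates actually vary with SD 2.95 (REML) and 2.90 (ML), against 3.01 for fixed effects.

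**The case against.** The strongest reply is that this is a modest preference between two defensible models. Much of that stands.

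- **Every harmful input is assumed.** The article gives no ICC, shares or clinic differences, and aligning clinic means with shares is a worst case. With equal shares nothing is lost.
- **Zero estimates are not an error rate.** They occur mostly when observed clinic differences are small, which is when pooling costs least.
- **Baseline adjustment helps.** Adding a baseline score to the Step 3 simulation (assumed correlation 0.5, same clinic gap at baseline) cuts the bias to about 0.3 to 0.8 points. Weighting may remove more.

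A reader might also infer four stronger things that the article does not support.

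- **That the random intercept gives no protection.** Both groups are recruited at the same sites, so it pulls the estimate toward the within-clinic comparison.
- **That the bias is 1.2 to 2.4 points.** That belongs to a model with no clinic term, which is not planned.
- **That type I error is about 15%.** That arises with a sandwich variance clustered on four clinics and a normal cut-off. The article states neither, and a t cut-off on 3 df restores about 5%.
- **That clinic is missing from the propensity score.** No factors are listed at all, and such a list may sit in the full plan. If clinic is among them, the confounding argument largely falls away.

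What the reply does not remove is that the article fixes the weaker clinic term in the outcome model, where the stronger one is available at little cost.

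**Conclusion.** The point holds as a cheap improvement to the primary analysis. Four clinics cannot support a usable clinic variance, and in a non-randomised comparison the random intercept gives partial, not full, protection against between-clinic confounding.

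If the BKK share runs from 20 to 60% across hospitals and clinic means span 5 to 10 points in line with it, about 0.7 to 1.1 points of bias remain. That is 7 to 11% of the planned difference of 10, with type I error of about 5 to 8%. A stronger imbalance gives up to about 1.7 points and 11%; equal shares give essentially none. These figures leave out weighting and, except where stated, baseline adjustment, both of which are planned and would be expected to reduce them. They show how sensitive the planned model is and do not predict the bias in this study.

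**What to change.** In the Module 1 outcome model, enter clinic as a fixed effect with three indicators and keep the random intercept for patient. Name clinic among the propensity-score factors. If robust standard errors accompany the weights, cluster them on patient and not on the four clinics. Change the sample size text to match: a two-level model with clinic as a fixed factor.

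The cost is three degrees of freedom and a few lines of text. The standard error is about 2 to 5% larger in the 20 to 60% scenario, and about 8 to 10% larger under strong imbalance. Inference becomes conditional on these four hospitals, which gives up little, since four sites could hardly support a wider claim. No further patients or data are needed.
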